## Abstract

*Background*: Up to 80% of patients who develop coronavirus disease-2019 (Covid-19) infection subsequently experience long covid/post-covid syndrome. The World Health Organization (WHO) has estimated that >770 million patients have been infected with Covid-19 globally. Even if only 10% of these patients develop long covid, > 75 million patients will suffer for a long period. Among the various symptoms of post-covid syndrome, fatigue is common, affecting up to 60% of the patients. As observed in other viral infections, elevated levels of inflammatory cytokines may play a role. Transcutaneous auricular vagal nerve stimulation (taVNS) is a noninvasive method that modulates the immune system via the central nervous system and has shown promising effects in autoimmune diseases and improving fatigue. In this pilot study, we investigated the feasibility of daily taVNS in patients with long covid-related fatigue. Additionally, the effects of taVNS on fatigue and quality of life will be analyzed. *Methods*: A total of 45 adult patients with long covid associated fatigue syndrome will be enrolled in this study, and will be randomized to the above-threshold-stimulation, below-threshold-stimulation, or sham-stimulation arms, after being informed that they will feel the stimulation. The above-threshold-group will receive a 4-week-long left-sided cymba conchae taVNS with 25 Hz, 250 µs pulse width 28s/32s on/off paradigm for 4 h throughout the day. The below-threshold group will receive stimulation below the sensational threshold, whereas the sham group will receive no stimulation following application of a non-functional electrode. The daily stimulation protocol will be recorded either manually or using the provided app. Three well-established questionnaires, the Multidimensional-Fatigue-Inventory-20, Short-Form-36, and Beck-Depression-Inventory, and the newly established Post-Covid-Syndrome-Score will be completed both before and after 4 weeks of stimulation. *Discussion*: The primary endpoint has been set as the patients’ average daily stimulation time after 4 weeks, while secondary endpoints include the effects of taVNS on fatigue and Quality of Live (QoL). As a non-invasive treatment option, taVNS may be a notable alternative for patients with post-covid related fatigue. *Trial registration*: This study was approved by the local ethics committee (23/7798) and registered (DRKS00031974) (see supporting information files). *Ethics & Dissemination:* The ethical justifiability of this study was supported by prior research demonstrating the safety of taVNS. Patients will be recruited by general practitioners, and written informed consent will be obtained. All data will be pseudonymized for collection and storage. The study results will be published in peer-reviewed journals with the aim of providing evidence of the potential of taVNS in long covid management. The study will be conducted in accordance with the principles of the Declaration of Helsinki.

## Introduction

Up to 80% of patients suffer from long-term consequences after recovering from a SARS-CoV2 infection, that hinder their reintegration into daily work and family life [1,2]. These limitations have prompted the recent publication of the German “Standing Guideline Commission of the Association of Scientific Medical Societies in Germany”(“Arbeitsgemeinschaft der Wissenschaftlichen Medizinischen Fachgesellschaften” - AWMF) guidelines for the rehabilitation of patients with coronavirus disease-2019 (Covid-19) [3]. In one study, fatigue was observed in 53% of 143 patients [4]. Fatigue is a well-known symptom of viral infections [5] which can significantly impact patients, particularly in patients who have had a Covid-19 infection [6]. This symptom can continue to affect patients for months after recovery from the infection [2,7]. The fatigue severity scale is a frequently used screening tool for fatigue [8], commonly used to diagnose chronic fatigue.

Invasive vagus nerve stimulation (iVNS) has been approved for the treatment of epilepsy and depression since the early the 1990s and 2000s [9]. Vagal activation through vagal nerve stimulation (VNS) leads to immunomodulation, which seems to have a positive effect on autoimmune diseases such as chronic inflammatory bowel disease [10], rheumatoid arthritis [11], and pancreatitis [12] in experimental settings.

Based on the anatomical observation that a specific part of the ear, the cymba conchae, is solely innervated by the vagus nerve [13–15], electrical stimulation of this region has been investigated as a noninvasive alternative to iVNS. Studies have shown that this transcutaneous auricular VNS (taVNS) leads to comparable brain activation as iVNS [16,17]. Furthermore, taVNS has been shown to positively influence epilepsy [18], depression [19], and cytokines in rheumatoid arthritis [20]. Further large-scale studies and compliance with the defined standards [21] are required to further investigate the effectiveness of taVNS under these conditions.

Owing to the pandemic, further research on the causes of fatigue has not yet been conducted, while the underlying causes of fatigue remain inconclusive. Although conflicting results have been published [22,23], existing research indicates that the development of fatigue is partly triggered by increased levels of pro-inflammatory hormones known as cytokines in the blood, while its severity seems to correlate with the levels of these cytokines in the initial phase of the disease [24]. Studies have further shown that Covid-19 infection leads to a massive increase in cytokines, known as the cytokine storm [25,26], resulting in elevated levels of interleukin (IL) 2, IL-4, and tumor necrosis factor-alpha [27]. Consequently, one Cochrane review demonstrated that IL-6 blocking medication could have a positive impact on the course of acute Covid-19 infection [28]. Overactivation of mast cells also seems to play a possible role in the development of long-term Covid [29], while D-dimer and C-reactive protein levels also appear to correlate with the occurrence of fatigue during the long-term Covid phase [30].

TaVNS has been shown to reduce inflammatory cytokines [31–33], modulate cardiac vagal tone [34], modulate arousal through central pathways [35] and positively influence depressive disorders [36,37], which may play a role in the development of long-covid associated fatigue. This modality has already been applied in pilot studies of patients with acute Covid-19 infection, where it has been shown to help lower cytokine levels [38], thus emphasizing the urgent need for further studies on non-invasive VNS in Covid-19 [39]. The effectiveness of taVNS on fatigue syndromes in systemic lupus erythematosus [40] and Sjögren’s syndrome [35,41] was also investigated in a recent clinical trial FatiVa [42]. However, whether taVNS reduces fatigue by reducing inflammatory cytokine levels or through a direct central mechanism remains unclear [43]. However, several studies have discussed the potential use of noninvasive vagal nerve stimulation in the treatment of long-covid, showing promising results [44–47]. The influence of VNS on olfactory function is currently being investigated; however, further research is warranted [48,49].

In summary, vagus nerve stimulation appears to have the potential to reduce the occurrence of fatigue and depression in long covid syndrome by modulating the immunosystem and influencing the central arousal pathways. As reintegration into daily life and work is of paramount importance in patients’ quality of life, and the healthcare or retirement system, we aimed to evaluate whether taVNS, which has few side effects, exerts a positive influence on the rehabilitation capacity and acceptance of treatment among long covid patients with fatigue syndrome.

## Materials and methods

### Inclusion criteria:

History of prior Covid infection within the last 36 monthsFatigue persisting for ≥ 3 months, with a score ≥4 on the FSS (Fatigue Severity Scale)Age > 18 yearsNo or stable treatment for depression for at least 4 weeks

### Exclusion criteria:

Severe psychiatric illness, such as schizophreniaAcute Covid infection within the last 14 days>8 points on the « Nurses’ Global Assessment of Suicide Risk » questionnaireImplanted vagus nerve stimulator or history of vagotomySignificant heart disease: bradycardia (e.g., sick sinus syndrome), heart failure, or a history of myocardial infarctionActive implants include pacemakers, defibrillators, neurostimulators, cochlear implants, and drug delivery devicesInability to understand the study planProgressive neurological disease (e.g., Parkinson’s, Multiple Sclerosis, epilepsy)PregnancyOther acute illnesses or conditions associated with fatigue (e.g., cancer, chemotherapy treatment, and autoimmune diseases)PolyneuropathyPresence of skin conditions, such as infection, psoriasis, or eczema in the treatment areaPresence of any anatomical anomaly that prevents successful placement of the ear electrodePresence of any serious illness that prevents successful participation in the study.

### Questionnaires

Three well-established questionnaires will be used: the ShortForm36 (SF36), the Beck Depression Inventory (BDI), and the Multidimensional Fatigue Inventory (MFI20). In addition, the newly established Post-Covid-Syndrome-Score (PCS Score) of the “National Pandemic Cohort Network” Consortium [50] will be included.

### Abortion criteria

Patients will discontinue participation if they present with any of the exclusion criteria.

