### Selection of patients and data collection

A total of 45 patients will be recruited and divided into three groups. Patients will be informed about the study through flyers and by their general practitioners, and will be provided with access to a website. Additionally, local support groups will be contacted and informed. On the website, questions regarding the inclusion and exclusion criteria will be asked anonymously, without data storage. At the end of the questionnaire, patients will be informed of whether they qualified for the study. In the case of study qualifications, patients will be provided with an email address where they can sign up to participate. Patients will be informed about the study aims and procedures by an investigator or certified medical professional. After obtaining written informed consent, data collection will be pseudonymized in the RedCap electronic case report form (eCRF) system of Ruhr-University-Bochum and will be General Data Protection Regulation (GDPR)-compliant. The RedCap system automatically randomizes patients into Verum-1, Verum-2, or Sham groups (n = 15 each). The patients will be instructed on how to use the simulator for 4 h per day, with at least 1 h of consecutive stimulation in the left ear. Patients will be asked to log all stimulation times manually in a diary. Because patients in the sham group will also receive the device’s user manual, which states that they should feel a tingling sensation in the ear, they will be instructed to use the highest stimulation intensity that is not perceptible to them. After adjusting the stimulation to this level, sham patients will receive a non-functional electrode that does not perform any stimulation. This approach is justified as the principle “more is better” does not apply to vagus nerve stimulation, and stimulation below the perception threshold could still, theoretically, have an effect.

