### Data analysis

The two-sided p-value of Fisher’s exact test will be used to evaluate the difference between the three groups (primary outcome is an incidence rate with patients who exceed a usage-time-threshold). Additionally, the two treatment groups will be descriptively compared with the placebo group, and between themselves. The rationale to use Fisher’s exact test is to compare binary data between groups (in total three two-group comparisons). The rationale for the Kruskal-Wallis rank analysis of variance is to avoid the potential influence of outliers and to handle unknown data distributions (normally distributed data are not expected).

Since three tests (each group compared with each other) are performed and the threshold for the p-value was set at an overall (studywise) alpha of 0.05, then three tests result in an Bonferroni-adjusted (comparisonwise) threshold of p/ 3 = 0.017. p-values below this threshold denote a statistical significant difference.

Secondary outcome measures included the MFI20, BDI, SF-36, and PCS-score, which were modified similarly to the primary outcome measures. BDI, SF36 and PCSS are other secondary measures which will be analyzed descriptively. Since those parameters are continous rank-analses of variance (Kruskal wallis tests) will be used. Descriptive statistics, such as means, medians, quantiles, and respective case numbers of the available data, will be reported. The between-group contrast will be reported as the mean difference with 95% confidence intervals. Additionally, a nonparametric estimation of the group effect (shift) using the Hodges-Lehmann estimator shift will be provided.

Successful acceptance and compliance will be defined as achieved when the acceptance criteria (average taVNS for 4 h/day) are met by at least 80% of patients. A total of 45 patients will be enrolled, with 15 assigned to each of the three groups: “sham”, “Verum-1”, and “Verum-2.” The decision to have 15 patients per group was based on feasibility, as well as from influence by studies that examined noninvasive VNS for sleep deprivation, lupus, and Sjoegren’s syndrome. Furthermore, the selected sample size was aligned with the recommended sample sizes for feasibility studies [51,52].

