**Fig 1 pone.0315606.g001:**
[figure not shown]
SPIRIT schedule of enrollment of the CoViva Study.

Stimulation will be conducted using the commonly chosen parameters in the literature, which have been successfully applied over a period of 20 weeks [54]. These parameters include a frequency of 25 Hz and a pulse width of 250 µs. These stimulation parameters will be preset in the commercially available, CE (Conformité Européenne, European equivalent to FDA) tVNS-L stimulator and cannot be changed. Stimulation will be applied throughout the day for 4 h using a 28s on/ 32s on/off schedule. Patients will be asked to download available Android and iOS apps, which will be paired with the stimulator via Bluetooth to document the daily stimulation time. Based on these records, patients will be able track when the recommended 4 h daily stimulation target day is reached. Although the stimulator will be turned off after 4 h of continuous stimulation, there is no automatic blocking of the stimulator after 4 h of cumulative stimulation, as only patients who understood the study protocol will participate, in accordance with the exclusion criteria. Additional negative effects of a stimulation lasting more than 4 hours have not been reported in literature – however, the likelihood of known side effects such as headache, ear pain, skin irritation or nausea [55] increases if stimulation lasts longer than 60min [56].

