### Study procedure

The study commenced on 1^st^ September 2023. As there is no central point of contact for patients with long covid, all participants were/will be informed about the study by their general practitioners. Contact will be established between general practitioner networks and local support groups. General practitioners can identify suitable patients based on the inclusion and exclusion criteria, and referred them to the study investigator. The two visits (“Visit 0” and “Visit 1”) and the telephone interview will subsequently be scheduled following consultation with the patient.

During the study period, participants will use the “tVNS Patient” app developed by tVNS Technologies GmbH (available for free in the respective app stores) to automatically document the frequency and duration of stimulations. Compliance documentation will be provided, as recommended in the 2020 consensus paper on noninvasive VNS [21]. Only the patient can access these data, which will be finally reviewed by a physician at the end of the stimulation period. All data will be stored exclusively on participants’ smartphones. The questionnaires will be entered and analyzed as electronic case report forms (eCRFs) in the RedCap system of the Department of Medical Informatics.

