#### Telephone interview after 7 days.

After 7 days, patients will be contacted by phone or email (if preferred) to inquire about their use of the stimulator, any side effects, or any potential questions they may have.

##### Visit 1

After 4 weeks, the patients will complete the questionnaires again. Personal data, including weight, will be collected, while data regarding the duration of stimulation will be retrieved from a smartphone. Subsequently, the stimulators will be returned. Patients who cannot attend visit 1 because of their health conditions will receive online access to the questionnaire section of the eCRF to complete it from home.

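### The stopping rule ends participation, not only stimulation, when a randomised patient newly meets an exclusion criterion, so that patient has no stated week-4 MFI20 or app read-out

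*Protocol article*

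**What the plan says.** All references are to the protocol article.

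- **Abortion criteria:** "Patients will discontinue participation if they present with any of the exclusion criteria". The section says nothing else.
- **Exclusion criteria:** the list includes conditions that can be new after enrolment: acute Covid within 14 days, pregnancy, a raised suicide-risk score, other acute illness linked with fatigue, and skin disease where the electrode sits.
- **Visit 0:** group assignment takes place here, before the 4-week stimulation phase.
- **Visit 1:** the questionnaires are repeated after four weeks, and "data regarding the duration of stimulation will be retrieved from a smartphone". Patients too ill to attend may complete the questionnaires online.
- **Study procedure:** on the app records, "Only the patient can access these data, which will be finally reviewed by a physician at the end of the stimulation period". Until then they are held only on the participant's phone.
- **Selection of patients and data collection:** "Patients will be asked to log all stimulation times manually in a diary".
- **Telephone interview:** "After 7 days, patients will be contacted by phone or email (if preferred) to inquire about their use of the stimulator".
- **Data analysis:** acceptance counts as achieved when "the acceptance criteria (average taVNS for 4 h/day) are met by at least 80% of patients". Descriptive statistics will be given with the "respective case numbers of the available data".

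**The concern.** A rule about discontinuing can act only on someone already enrolled, and assignment is made at Visit 0. The rule therefore removes randomised patients because of later events. Stopping stimulation is sensible for most of the criteria. Ending follow-up is a separate step that safety does not require: none of these conditions in itself prevents a questionnaire or a reading of the app, and acute Covid is transient.

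Two results could suffer. One is the MFI20 comparison, which the sample size section calls the most important secondary endpoint. The other is the acceptance rate, which is the purpose of the pilot. The Safety section also says that the pilot is to inform expected adherence and dropout for a larger study. Exits imposed by the rule would be mixed with exits that patients chose, and the two mean different things for planning.

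An analysis plan can define who is analysed. It cannot recover questionnaires that were never collected because participation had ended.

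**Working it through.** **The plan's own figure.** Sample size calculation: 36 evaluable patients (3 × 12), a margin of 10% to 20%, 45 enrolled. 36/(1 − 0.20) = 45, so the stated total is reproduced at the upper end of the margin (36/0.90 = 40 at the lower end). The margin covers 45 − 36 = 9 losses, and a few rule-forced exits fit within it. The issue is missing outcomes in randomised patients, not the sample size.

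**What remains for a removed patient.**
- Week-4 MFI20: stated only at Visit 1. The online route is for patients whose health prevents attendance and is not extended to those whose participation has ended.
- App time: retrieved at Visit 1, and the online route covers questionnaires only.
- Diary: exists, but no collection point is given.
- Day-7 contact: covers the first week at most.

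Stimulation time thus has partial fallbacks. The week-4 MFI20 has none.

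**How many.** The article gives no rate for such exits. Its nearest figure (Safety) is 2.6% stopping for side effects, from cervical and auricular stimulation together: 0.026 × 45 = 1.17 patients. This does not measure exits under the rule. Each patient is 1/45 = 2.2% of the sample and 1/15 = 6.7% of an arm.

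**The 80% criterion.** If all 45 count, 0.80 × 45 = 36 successes are needed. Suppose k removed patients, who would otherwise count as not meeting the target, are left out:

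| k | Needed if left out | Needed if all count | Counts where the verdict differs |
|---|---|---|---|
| 1 | 0.80 × 44 = 35.2, so 36 | 36 | none |
| 2 | 0.80 × 43 = 34.4, so 35 | 36 | 35 only (35/43 = 81.4%; 35/45 = 77.8%) |
| 5 | 0.80 × 40 = 32 | 36 | 32 to 35 |

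**How a stopped patient counts.** With 4 h/day until a stop at day 14, the average over the planned 28 days is 4 × 14/28 = 2.0 h/day, which fails. Over the 14 active days it is 4.0 h/day, which passes.

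**MFI20.** Assume that one removed patient differs by D units from the other 14 in the arm. The mean of 15 then differs by D/15 from the mean without that patient. For D = 10 to 20 (an assumption; the article gives no basis for it), this is 10/15 = 0.67 to 20/15 = 1.33 units. Against the smaller planned shift of 5 units, that is 13% to 27%.

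**The case against.** **This is a condensed article.** A fuller approved version is mentioned under Ethics and regulatory aspects, and it may say how stopped patients are followed. That is fair for details that are merely absent. Here the article states a rule, and its object is participation. The online option shows a wish to keep collecting data from ill patients, but it is not offered to patients who have been discontinued.

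**A reader might infer that the rule removes more verum than sham patients.** The reasoning would be that "the likelihood of known side effects such as headache, ear pain, skin irritation or nausea [55] increases if stimulation lasts longer than 60min", that the regimen is 4 h per day, and that the sham electrode passes no current. The article does not support that as a finding. Skin irritation is not the listed exclusion criterion, which names infection, psoriasis and eczema as examples. Sham patients also wear an ear electrode, and no rates by arm are given. A difference is possible, no more.

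**A reader might also infer that removed patients leave the 80% denominator.** The text sets no such rule. It says only that patients are counted, and the remark about available data concerns the numbers shown beside descriptive statistics. The table above shows what would follow if they were left out, not what the plan prescribes.

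**The effect is small, and the analysis limits it further.** This stands. One or two exits hardly move the verdict. The Kruskal-Wallis test and the Hodges-Lehmann estimate are less sensitive to a single patient than the mean, although a mean difference with a confidence interval is also planned.

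**Counting a patient stopped for unrelated Covid as non-accepting is a choice of estimand, and a fatigue score during acute illness reflects that illness.** Both points stand. They argue for showing results both ways. They do not argue against collecting the data.

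**Conclusion.** The point holds in limited form. Followed literally, the rule ends follow-up for randomised patients who newly meet any exclusion criterion, and they then have no stated week-4 MFI20 or app read-out. The loss can be avoided and cannot be repaired at analysis.

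The number affected is unknown and probably small. The figure of about one patient rests on a borrowed 2.6% that measures something else. The shift of 0.7 to 1.3 MFI units per removed patient rests on an assumed difference of 10 to 20 units. Bias linked to the arm is not established, and the plan does not say that stopped patients are excluded from the acceptance rate. This is an inexpensive improvement worth making, not a defect that threatens the trial.

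**What to change.** Replace the sentence under Abortion criteria with: *A patient who newly meets an exclusion criterion after randomisation stops stimulation but, unless consent is withdrawn, remains in follow-up. App and diary stimulation times are read out, and the week-4 questionnaires are completed at Visit 1 or online.*

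Add under Data analysis:
- Rule-forced stops are reported separately from patient-chosen ones, by arm.
- MFI20 is shown with and without patients stopped under the rule.
- The 80% acceptance rate is reported with all randomised patients in the denominator and, as a sensitivity analysis, without stops unrelated to the device. State the period over which daily time is averaged, because it decides how a stopped patient counts.

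Cost: a few extra contacts with stopped patients, since Visit 1 and the online questionnaires already exist. The study began on 1 September 2023 under an approved version, so a short ethics amendment would probably be needed. The acceptance rate may come out slightly lower. The sample size does not change.
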